#### Psychological assessment

3.6.4

Insights into various dimensions of the participants’ behavioural, psychological, emotional, and social functioning will be provided by both self-report and parent-report questionnaires, as summarized by **Table 2**.

**Table 2 T2:** Questionnaires used to assess participants psychological domains.

Tool name	Constructs Assessed	Type	Outcome
Child Behavior Checklist for Ages 6–18 (CBCL 6–18)	Behavioural and emotional symptoms	Parent-report	T-Scores
Pediatric Quality of Life Inventory 4 (PedsQL version 4)	Physical, Emotional, Social, and School Functioning	Parent/self-report	Percentual Scores
Adaptive Behavior Assessment System-Second Edition (ABAS-II)	Social Adaptive domain	Parent-report	Standard Scores
Social Responsiveness Scale (SRS)	Social awareness, social cognition, social motivation and social communication	Parent-report	T-Scores
Eating Disorders Questionnaire in Childhood (EDQ-C)	Eating disorders, attachment patterns, anxiety and mood disorders, relational and behavioural difficulties	Parent/self-report (≥ 8 years old)	Standard Scores, Percentile Ranks

To investigate participants’ behavioural and emotional symptoms, the Child Behavior Checklist for Ages 6–18 (CBCL 6–18; 58) will be administered. The CBCL is a standardized parent-report questionnaire, comprised of 8 syndrome scales (anxious/depressed, withdrawn/depressed, somatic complaints, social problems, thought problems, attention problems, rule-breaking behaviour, and aggressive behaviour), 3 broadband scores (internalizing and externalizing problems, and total problem), DSM-oriented scales (affective problems, anxiety problems, somatic problems, attention deficit/hyperactivity problem, oppositional defiant problems, conduct problems), and the 2007 Scales (sluggish cognitive tempo, obsessive-compulsive problems, post-traumatic stress problems). For each subscale raw scores will be converted in T-scores (M = 50, SD = 10).

The Pediatric Quality of Life Inventory (PedsQL version 4; 59) is a widely used tool in studies involving children with obesity to measure key dimensions of health and quality of life, as outlined by the WHO (60). Developed through focus groups, cognitive interviews, pretesting, and field-testing (61), the PedsQL Generic Core Scales 4.0 includes domains of Physical, Emotional, Social, and School Functioning. Both child self-report and parent-report formats will be administered. Total Score and Psychosocial Health Summary Score will be calculated as percentages.

Adaptive skills will be assessed using the standardized parent-reported Adaptive Behavior Assessment System, Second Edition (ABAS-II; 62). In particular, the social skill domain will be investigated through the Social Adaptive Composite (SAC), which summarizes performance across the Leisure and Social skill areas. Raw scores will be converted into standardized weighted scores (M = 10, SD = 3) and standard scores (M = 100, SD = 15).

The Social Responsiveness Scale (SRS; 63) is a standardized parent-report measure frequently used with children and adolescents between the ages of 4 and 18 years (64) to screen subtle social communication deficits. The SRS generates 5 subscales: social awareness, social cognition, social motivation and social communication. Raw scores will be converted to gender-normed T-scores (M = 50, SD = 10).

The Eating Disorders Questionnaire in Childhood (EDQ-C; 65) is a standardized tool used for the early identification of eating disorders in children, assessing comorbidities with attachment patterns, anxiety and mood disorders, as well as relational and behavioural difficulties. It includes a self-report version for children aged 8 and older, and 2 parent-report forms based on the child’s age (4–7 and 8–12 years). For each diagnostic category, raw scores will be calculated and converted into standard score and percentile ranks (< 90 = within normal range, > 95 = clinically significant, > 99 = pathological).

#### Neuropsychological assessment

3.6.5

The Colored Progressive Matrices (CPM; 66) will serve as a measure of non-verbal fluid intelligence due to its minimal reliance on language skills. The global Intelligence Quotient (IQ) will be considered in the analysis (M = 100, SD = 15).

The N-back (67) is a computerized task testing both visuo-spatial and verbal working memory. In the visual-spatial condition, participants view a series of visual stimuli (blue boxes) positioned randomly on the screen. Following a training phase, participants must indicate whether the location of each box matches that of the preceding 1 (level: 1-back). When response accuracy reaches or exceeds 80%, the difficulty level of the n-back is increased (for example, advancing from 1-back to 2-back). Similarly, the verbal condition requires participants to listen to a continuous stream of letters and the goal is to decide whether each letter matches the 1 heard immediately before (level: 1-back). Exercise progression follows the same protocol as the visuo-spatial condition.

The Continuous Performance Test-II (CPT-II; 68) is a computerized standardized measure of sustained performance that provides indices related to the attentional domain as well as executive functions, such as inhibitory control. Participants are instructed to press the spacebar when any letter except the letter *“X”* appears on the screen. Reaction Time (RT) is measured from the point at which any letter other than *“X”* appears on the screen until the spacebar is pressed (Go trial). No-Go trials occur when an *“X”* is presented. To mitigate the impact of repeated testing familiarity, a 3-minute practice will be presented prior to starting the CPT-II. Accuracy, reaction times in milliseconds, and Reaction Time Variability (RTV) in milliseconds will be included in the analyses.

To assess episodic long-term memory, the Verbal and Visual-Spatial Learning tasks from the standardized Battery for the evaluation of Memory (PROMEA; 69) will be administered. The Verbal Learning Task consists of a list of 15 semantically unrelated words that is presented orally for 3 consecutive trials. After each presentation participants will be asked to immediately recall as many words as possible, in any order; the number of words recalled across the 3 trials will be scored. Fifteen minutes after the third trial, participant will be requested to recall as many presented words as possible; the number of elements correctly recalled will be scored. Similarly, in the Visual-Spatial Learning Task, 15 figures of common objects positioned within 4 quadrants are presented in the study phase. After a 1-minute interval begins the test phase, where the target stimuli are presented individually, and the participant is asked to indicate the correct position. The test is repeated 3 times and, as in the verbal task, the number elements correctly recognized across the trials will be scored. Fifteen minutes after the third trial the test phase only will be presented again to assess the delayed recognition, scoring the number of elements correctly recalled. For each index, raw scores will be calculated and converted into standard score and percentile ranks.

The Forwards and Backwards Digit Span and the Corsi Block-Tapping tests from the standardized Battery for Neuropsychological Evaluation of Children (BVN 5-11, 70) will be used to assess verbal and visuo-spatial short-term memory and working memory. In the Digit Span test participants are asked to repeat an increasing sequence of numbers, in the same or in the reversed order as presented by the experimenter. The score is determined by the number of items correctly recalled. A similar procedure is used with the Corsi Block-Tapping test, which consists of blocks on a wooden board. Participants have to observe sequences of blocks tapped by the experimenter and then immediately reproduce them, in the same or in the reversed order. Raw scores will be converted into z-scores based on the mean and standard deviation of the normative sample.

The Movement Assessment Battery for Children-2 (MABC-2; 71) will be used to assess participants gross and fine motor skills. This battery produces a total score and 3 component scores: a) the Manual Dexterity component evaluates fine motor skill; b) the Aiming and Catching component assesses the coordination of fine and gross motor skills; c) the Balance component assesses gross motor skills and includes a static balance task and 2 dynamic balance tasks. Raw scores will be converted into standard scores (M = 100, SD = 15) and percentile ranks.

In order to assess visual-motor skills the standardized Test of Visual Motor Integration (VMI; 72) will be employed. This test comprises 3 components: a) the Visual Motor Integration component, where children are required to imitate and copy a series of increasingly complex forms; b) the Visual Perception, that requires participants to identify matching forms when presented with similarly shaped forms; c) Fine Motor Coordination component, which involves children’s ability to connect dots and stay within lines of the forms. Raw scores will be converted into standard scores (M = 100, SD = 15) and percentile ranks.

By administering meals to children, it is possible to assess changes in satiety sensation. When comparing caloric and macronutrients intake at T0, T1 and T2, differences in food consumption - both in terms of quality and portions sizes - will be analysed. This will help determine the effectiveness of nutritional intervention during the first 8 weeks and the maintenance period.

##### Ex Vivo measures

3.6.6.2

Since direct assessment of leptin sensitivity in the central nervous system is not feasible in humans, we will evaluate peripheral leptin sensitivity ex vivo using PBMCs. Lymphocytes express the active form of the leptin receptor, and their responsiveness to leptin has been used as a proxy for central leptin sensitivity (36). The use of this proxy is further supported by evidence from animal studies, where a lower value of the food intake/leptin levels index correlates well with more direct measures of leptin sensitivity. These include detailed assessments of food intake following exogenous leptin administration and evaluations of leptin signalling, such as the expression of phosphorylated STAT3 in the arcuate nucleus of the hypothalamus (30, 79, 80).

PBMCs will be collected from the same individuals before and after the intervention and exposed to recombinant leptin to assess intracellular signalling activation. The primary leptin effector pathway is JAK2-STAT3, though ERK1/2 activation has also been reported among others (81). The activation of these pathways will be measured using immunoassays such as Enzyme Linked Immunosorbent Assay (ELISA) and Western blot, quantifying the ratio of phosphorylated to total protein levels for each intracellular effector. To mitigate the potential bias arising from inter-individual variability in lymphocyte proportions, we will normalize our signalling data by the lymphocyte counts obtained from each participant’s complete blood count with differential. Specifically, we will express our results as [e.g., fold change relative to baseline per 10^6 lymphocytes] or include the lymphocyte percentage as a covariate in our statistical models to account for this compositional variation. This approach will allow us to better discern the effects of leptin despite the use of a heterogeneous PBMC population.

Therefore, in addition to investigating the activation of STAT3, the main intracellular effector of leptin signalling, our research plan will analyse: 1) the PI3K–Akt Pathway, a major molecular pathway associated with metabolic regulation, insulin signalling, glucose homeostasis, and neuroendocrine function (82); 2) the AMPK pathway, which is known to be activated directly by leptin in peripheral tissues (83) but inhibited in the hypothalamus; and 3) the function of SOCS3, a negative regulator of the JAK2-STAT3 signalling pathway relevant to the leptin resistance state (84). We will aim to assess protein expression and phosphorylation of key components within these pathways in response to our interventions.

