## Hypothesis and aims of the resilient project

2

The present project hypothesizes that the combination of ST and CT with Intensive Health Behavior Treatment (IHBT; 26), which includes PA and dietary interventions, will lead to an improvement in leptin sensitivity in children following treatment for overweight and obesity.

Since direct assessment methods used in animal models are not feasible in humans, this study will rely on alternative proxies previously used to evaluate leptin sensitivity. In humans, except for rare pathological conditions such as congenital leptin deficiency or lipodystrophy, leptin administration is not approved. In rodent models, leptin sensitivity is typically assessed through a more direct and rigorous procedure. This involves administering recombinant leptin, followed by measuring food intake and/or evaluating leptin signalling in the brain. The latter is achieved by analysing the activation of intracellular effectors, such as STAT3 and Extracellular signal-regulated protein kinases 1 and 2 (ERK1/2), after hypothalamic dissection.

In our participants, we will estimate leptin anorectic effect by calculating the ratio between circulating leptin levels and total calorie intake measured during an ad libitum laboratory meal. This ratio will serve as the primary outcome to assess changes in leptin sensitivity. Additionally, molecular analysis will be conducted on Peripheral Blood Mononuclear Cells (PBMCs) to monitor the activation of leptin signalling pathways, as previously performed in other human studies (36).

As a secondary outcome, we will explore the association between changes in leptin sensitivity and improvements in cognitive measures, such as spatial and verbal long-term memory and spatial and verbal working memory.

Additionally, some supplementary endpoints will be measured at each time point to provide a more comprehensive understanding of the intervention’s effects.

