### Sample size

3.4

The sample size for the 3-arm study was determined considering the different decrease of leptin values (an indirect estimate of the primary endpoint leptin sensitivity), following the intervention (mean values of 10 mg/dL in the IHBT group compared to 6 mg/dL in the ST+IHBT or CT+IHBT group, SD = 4). An effect size of 1 was considered as clinically relevant (comparing CT+IHBT group vs. IHBT group and ST+IHBT group vs. IHBT group using Student’s t-test).

Pairwise comparisons will be performed with a significance threshold of p < 0.017 to account for multiple comparisons (3 comparisons), using Bonferroni corrections (p = 0.05/3). To achieve a significance level of alpha equal to 0.017 and a study power of 95%, 30 patients per group are required; considering a 30% dropout rate during follow-up, the plan is to recruit a total of 120 participants (40 per group). Missing data will be excluded from the statistical analyses; otherwise, if the proportion of missing values does not exceed 20%, we will use a mean substitution method, or a multiple imputation method (as for example KNN) as needed.

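### Dividing the ex vivo phosphorylated/total ratio by the blood lymphocyte count, one of two normalisations left open, cannot correct for PBMC composition and can turn a count change into an apparent signalling change

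*Protocol article*

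**What the plan says.** Section 3.6.6.2 (Ex Vivo measures) of the protocol article sets out the assay and its scaling in four steps.

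- Material: "PBMCs will be collected from the same individuals before and after the intervention and exposed to recombinant leptin".
- Readout: "quantifying the ratio of phosphorylated to total protein levels for each intracellular effector".
- Reason for a further adjustment: "To mitigate the potential bias arising from inter-individual variability in lymphocyte proportions".
- The adjustment: "we will normalize our signalling data by the lymphocyte counts obtained from each participant’s complete blood count with differential". The next sentence specifies it: "Specifically, we will express our results as [e.g., fold change relative to baseline per 10^6 lymphocytes] or include the lymphocyte percentage as a covariate".

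The bracketed example is unfinished, the two forms are joined by an 'or', and the section does not say whether baseline means the T0 visit or a sample not exposed to leptin. On the role of the measure, section 2 names the in vivo leptin and calorie-intake ratio as primary outcome and then adds: "Additionally, molecular analysis will be conducted on Peripheral Blood Mononuclear Cells (PBMCs) to monitor the activation of leptin signalling pathways".

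**The concern.** A phosphorylated/total ratio is formed within one sample, so the quantity of cells assayed already cancels. What does not cancel is the mix of cell types, and that is what the protocol says it wants to correct. A lymphocyte count from whole blood does not measure that mix. It gives lymphocytes per volume of blood, not the number or share of lymphocytes in the isolated PBMCs. Dividing by it brings a quantity from outside the assay into the index.

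At stake is the interpretation of the molecular evidence. A change in blood count between T0 and T1 could be reported as a change in leptin responsiveness. The Discussion also offers the ex vivo procedure for reuse in evaluating anti-obesity medications, so a faulty index would be carried forward. With two non-equivalent forms open, the choice could also be made after the results are known.

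**Working it through.** The protocol states no figure for this measure, so there is none to reproduce. The 1/count relation is exact algebra. All lymphocyte figures below are assumptions, because the document gives none.

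**1. Index divided by the count.** Let R be the phosphorylated/total ratio and L the blood lymphocyte count, with index I = R/L. If R does not change, I(T1)/I(T0) = L0/L1. Take R = 0.30 and L0 = 3.0 (×10^9/L, assumed); the units drop out of the relative change.

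| L1 | Change in count | L0/L1 | Apparent change in index |
|---|---|---|---|
| 2.7 | −10% | 1.111 | +11.1% |
| 2.4 | −20% | 1.250 | +25.0% |
| 3.3 | +10% | 0.909 | −9.1% |
| 3.6 | +20% | 0.833 | −16.7% |

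**2. Does the way the fold change is built matter?** Take stimulated 0.30 and unstimulated 0.15, a fold change of 2.0 at both visits.

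- Fold change first, then divided by the count: 2.0/3.0 = 0.667 at T0 and 2.0/2.4 = 0.833 at T1. This is again +25% with no change in signalling.
- Both values divided by the same count first: (0.30/3.0)/(0.15/3.0) = 2.0 and (0.30/2.4)/(0.15/2.4) = 2.0. The count cancels and nothing has been corrected.

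Neither construction corrects for lymphocyte proportions.

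**3. Is some composition correction justified?** Let the lymphocyte share f of the PBMCs fall from 0.8 to 0.7, with lymphocyte ratio 0.3, non-lymphocyte ratio m and equal total protein per cell. The sample ratio is 0.3f + m(1 − f).

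- m = 0: 0.24 falls to 0.21, or −12.5%. Dividing by f gives 0.30 at both visits and removes the shift.
- m = 0.3: 0.30 at both visits. Dividing by f gives 0.375 and 0.429, a false +14.3%.

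Composition can matter, but even division by the correct share is right only if the other cells do not respond. A covariate does not impose that condition.

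**4. Comparison between arms.** If counts fall by 10% in every arm, each index is multiplied by 1/0.9 and the ratio between arms is unchanged. A false arm effect needs counts to move differently by arm. A null simulation shows what would then happen. It used 4000 runs, 30 per arm and alpha 0.017 (both figures from section 3.4). It assumed a count 10% lower in one arm, log-scale SD of 15% for count and for ratio, and independence of the two. Rejection rates were 1.6% for the plain ratio, about 31% for ratio/count, and 1.6% for the ratio with the count as covariate.

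**5. Noise.** With ratio and count independent, log-scale variance is multiplied by [ln(1 + CVr²) + ln(1 + CVc²)]/ln(1 + CVr²). For CVr = 0.40 and CVc = 0.15 this is 1.15; for CVr = CVc = 0.30 it is 2.0. The increase is thus 15% to 100% over these assumed values.

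**6. The covariate form.** Assume differentials (neutrophils/lymphocytes/monocytes) of 50/40/8 and 60/32/6.4. Lymphocyte percentage falls from 40 to 32, by a fifth. The lymphocyte share of mononuclear cells is 40/48 = 0.833 and 32/38.4 = 0.833, unchanged. Neutrophils are not part of a PBMC preparation but they move this covariate.

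**The case against.** The strongest reply has five parts.

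- Division is not settled. A reader might infer from the normalisation sentence that the ratio will certainly be divided by the count. The text does not support that, since a covariate is offered as the alternative and divides nothing. This stands.
- A correction for composition is legitimate. A reader might call the second step redundant because the ratio already cancels cell quantity. Step 3 shows that the ratio does not cancel composition, so the fault is the divisor and not the wish to adjust. This stands too.
- Bias between arms is not shown. All arms receive the same diet and physical activity programme, and no figure in the document suggests that counts would shift differently by arm. The 31% rests wholly on an assumed difference. The noise range assumes independence, and a positive correlation between ratio and count would shrink or reverse it. The differentials in step 6 were chosen to make the contrast visible. All of this stands.
- The data may not all be ratios. Section 3.6.6.2 also plans protein expression, including SOCS3. This does not rescue the divisor, because a whole-blood count is not the number of cells in the assay either.
- Choosing between scaling and a covariate may be left to an analysis plan that is not shown. That is fair for the choice alone. But the article itself states normalisation by the blood count, and that rule does not meet the aim given in the same sentence.

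**Conclusion.** The concern holds for the count-division form. It does not serve its stated purpose under any of the constructions examined: the index either moves with 1/count (+11% or +25% for a 10% or 20% fall with signalling unchanged) or the count cancels and nothing is corrected. The first result is exact wherever the division survives the fold change. How large the count changes will be cannot be told from the document. The covariate form does not create the artefact, but whole-blood lymphocyte percentage is a weak measure of PBMC composition. Two non-equivalent forms and an undefined baseline remain open.

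A reader might go further and conclude that the arm comparison is biased or that the main result is at risk. Neither follows. Bias between arms needs counts to change differently by arm; without that, division mainly adds noise and distorts within-person change. The primary outcome is the in vivo ratio, and the sample size in section 3.4 does not rest on the PBMC data. The effect is limited to a supporting measure.

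**What to change.** In section 3.6.6.2:

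1. Delete the scaling per 10^6 lymphocytes and the bracketed placeholder.
2. Define baseline as either the T0 visit or the sample not exposed to leptin.
3. Analyse the undivided phosphorylated/total response, comparing arms with its T0 value as covariate.
4. Name one composition covariate: lymphocytes/(lymphocytes + monocytes) from the planned blood count differential. It is still a blood-based proxy for the isolated sample, but it leaves neutrophils out.
5. Because a T1 value of that covariate is measured after randomisation, report the result with and without it.

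For the scaling and the covariate, the cost is wording only, since the assays and the differential are already planned. If baseline is defined as the unexposed sample, the sponsor should confirm that such an aliquot is part of the assay, because the article does not say so.
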